## Abstract

**Background**: The major determinant to the well-being of infants and young children (IYC) is their feeding practices. These practices are the responsibility of both parents, meaning that fathers have an equal role to mothers. Fathers’ involvement can have an impact on the overall health of the children. Despite this, paternal involvement towards IYC feeding (IYCF) have not been studied adequately.

**Methods**: This randomized control trial (n=120) will be conducted among fathers of infants (children aged <1 year) and young children (children aged 12-23 months) in selected households in Dakshina Kannada District of the southern Indian State of Karnataka. The study will be conducted after an initial baseline assessment on awareness, attitude and involvement of fathers in IYCF. Fathers with scores less than the 50
^th^ percentile in the practice component will be categorized as fathers with poor involvement and will be potential participants for the trial. A visual module will be developed and validated for improving paternal involvement in IYCF. Using a simple randomization technique, the participants will be allocated to modular intervention and control group (1:1 allocation). Each participant in the intervention arm will be visited once a month to implement the module, for six months on a one-to-one basis. Following the intervention, a post-test assessment will be done for both groups to measure the level of paternal involvement in IYCF.

**Ethics and dissemination**: Approval has been obtained from the Institutional Ethics Committee of Kasturba Medical College, Mangalore, India. The dissemination plans include scientific conferences and publication in scientific journals.

**Registration**: The study is registered with Clinical Trial Registry of India (
CTRI/2017/06/008936).

## Introduction

Feeding practices are one of the major determinants of the survival and wellbeing of children
^1^. Providing good nutrition to a child is the responsibility of both parents. Fathers are proficient caregivers; their positive involvement along with mothers in child feeding and rearing is associated with overall health outcomes
^2^. 

The currently available literature points towards the good impact of fathers’ involvement in infants and young children feeding (IYCF) and rearing on the health of their children
^3^. Also, the manner in which fathers assist and support their spouses in terms of child nutrition determines long-term effects
^4^. It has been documented that such positive behaviour from fathers results in a lower BMI among adolescent girls
^4^. Several strategies have been tried to enhance IYCF, including breastfeeding, such as establishing standards in providing maternity services through building public awareness using mass media, peer-support interventions, and health care provider driven initiatives providing maternal support
^5^. Observational studies have documented that the early provision of support from fathers and their active participation in breastfeeding practices, which could happen with adequate knowledge and a positive attitude, had effects on the initiation and overall duration of breastfeeding
^5^.

There are many socio-demographic factors playing an important role in paternal involvement in infant feeding practices, but there is lack of evidence to suggest the extent and determining level of paternal involvement
^6–
8^. Also, the module-based interventions for fathers to enhancing their involvement in IYCF have not been tested.

There are not many documented studies from India in this regard. This study would provide insight about the above stated priority areas and help investigators to develop strategies to enhance infant and young child nutrition, provide a modular intervention to fathers on IYCF, and then evaluate the intervention.

### Review of literature

Fathers play an important supporting role in overall maternal and child health
^9^ and their views of child-feeding practices influence development of the child and eating behaviour
^10–
12^. As a result of changes in societal norms, fathers’ involvement in childcare has increased compared to the level a few years ago. Increased involvement is influenced by several sociocultural, behavioral, hormonal, and neural factors
^13^. With the birth of a first child, a man enters the stage of fatherhood; which is a crucial and challenging period
^14^. If this entry to fatherhood becomes smoother, then the likelihood that the father being more involved in childcare is higher. This can happen with adequate knowledge transfer to the fathers of young children and prospective fathers
^13^. However, there are limited studies that have been done among fathers regarding their involvement in IYCF
^11^. In the Indian scenario, the evidence related to paternal involvement and measures for its enhancement is scant. The focus of interventions and studies related to child feeding are mostly on mothers, since mothers spend the most amount of time with children than anyone else in the family
^10^.

Across different regions of the world, studies done on fathers of young children were mostly of exploratory nature to assess the factors determining IYCF practices, qualitative assessments, couple-oriented interventions, family-based interventions,
*etc*. This limited involvement from the fathers’ side were influenced by several region- and culture-specific challenges they faced
^3,
9,
15,
16^. However, in countries like the UK, it was made a strategic priority to enhance breast feeding practices and it was realized that this could be achieved with a “strong social support from their partner”
^17^. It was also felt that fathers need informed guidance in supporting their spouses on breastfeeding and IYCF
^17^. There is no consensus on measuring male involvement and few beliefs exist that imply male involvement could be a threat to women’s empowerment and autonomy in terms of child rearing practices
^18^. Across the studies, there were felt needs from mothers and fathers of the young children regarding increasing the paternal involvement in the child feeding and care. Behaviour Change Communication strategies have been frequently used among mothers. Such strategies, when centered around both the parents have a higher effect on the father’s knowledge and involvement in child feeding, as compared to targeting mothers only. An increase in knowledge, however, may not have the desired impact on IYCF practices
^19^. 

Maycock
*et al.* carried out a randomized control trial (RCT) in Perth, Western Australia, known as the Fathers Infant Feeding Initiative (FIFI Study). The trial evaluated the effect of an antenatal paternal education session and spousal support during the postnatal period, targeted at fathers during the antenatal and postnatal period of their spouses. The study reported a significant increase in breastfeeding rate at 6 weeks. They also reported a correlation between a higher age of fathers and a high socio economic status with higher rates of breastfeeding at six weeks
^20^. Abdullahi
*et al.*, in Somalia, reported a quasi-experimental study in 2019, commissioned by Save the Children International (SCI), aimed at assessing the effects of peer counselling by Mother-to-Mother (M2M) and Father-to-Father (F2F) support groups on IYCF practices. They observed that there was IYCF knowledge growth, improvement in practices of breastfeeding and diet diversity among intervention arms. Since the follow up duration was short, there was no noticeable change in the nutritional status of children
^21^. 

In Japan, Ito
*et al.* reported an inverse relation between infant care by fathers and breastfeeding during the early infancy (first 6 months of life); fathers’ likelihood of involvement was higher with higher education status, being unemployed and nonsmoking
^3^. Pisacane
*et al.*, in Naples, Italy, investigated the effect of providing support to fathers in identifying their role in IYCF and teaching them to take care of most common lactation problems. They found that this intervention would result in higher rates of full breastfeeding at 6 months
^5^. Sherriff
*et al.*, in Southern England, studied the main attributes of father support in relation to breast feeding. They identified knowledge, attitude and involvement in decision-making as key factors towards successful breastfeeding practice
^22^. 

In rural Kenya, the quasi-experimental study with pre- and post-test observations conducted by Thuita
*et al.*, studied the impact of engaging fathers or grandmothers in improving diets of mothers and IYCF feeding practices through “parallel peer education dialogue groups with fathers and grandmothers.” They reported success in bringing increased paternal engagement in IYCF
^23^. 

One study conducted among 210 father-young child dyads in Bangalore, India, in 2020, by Inbaraj
*et al.*, aimed to “explore paternal child-feeding patterns, their involvement in feeding, and its association with level of malnutrition in the slums”. The overall involvement in child feeding and rearing was shown by nearly half of the study participants. Religion, family types, and individual income were factors associated with poor involvement of fathers in child feeding
^10^. 

In 2014, Khandpur
*et al.* reviewed the existing evidence on child feeding research in 20 studies, which included fathers’ feeding practices and their characteristics and correlations. They included studies which reported the feeding practices of fathers and/or primary care givers towards children aged up to 18 years. Most of the studies reported self-reported child feeding practices without a specific paternal validation. There were also studies reporting fathers pressuring their children to eat. Paternal and maternal feeding practices varied, wherein fathers monitored less and put more limitation to access to child’s food in comparison to mothers. Body fat of children was associated with fathers’ feeding practices
^11^. This review also brought out the paucity of literature on fathers’ child feeding practices.

### Aim of the study

To assess the effectiveness of a module-based intervention for improving the paternal involvement in IYCF.

### Objectives

1. To design and develop an educational module for the fathers on improving father’s IYCF practices and support.

2. To evaluate the effectiveness of module in improving the level of paternal involvement in IYCF

## Methods

Version: 1.0 (22-12-2020).

### Background information of the study area

The study area will be in the Dakshina Kannada District in the southern part of Karnataka State in South India. Regarding health care facilities, it is a progressing area. According to the 2011 Census report, the population of this area was 2,083,625, with a literacy rate of 88.62%
^24^. The current study is being done by the Department of Community Medicine, Kasturba Medical College, Mangalore, Manipal Academy of Higher Education, Manipal, India.

### Study setting

Community healthcare settings in Dakshina Kannada District, Karnataka State, India.

### Study design

The study will be a unblinded parallel group RCT. This study will follow the Consolidated Standards of Reporting Trials (CONSORT)
^25,
26^. The study flow according to CONSORT guidelines is depicted in the
*Extended data*
^27^. This study protocol is reported along with Standard Protocol Items: Recommendations for Interventional Trials (SPIRIT) Guidelines
^28^. A completed SPIRIT checklist can be found in the
*Reporting guidelines*
^27^.

### Study population

Fathers attending to infants (children aged <1 year) and young children (children aged 12–23 months) in selected households belonging to the geographical areas covered by public health care institutions of Dakshina Kannada District will be included. Households will be identified through records maintained in at public health care institutions. At the time of visit to their houses, their identity will be verified, along with confirmation of the age of their child.

### Sample size

With anticipated improvement in the paternal involvement of IYCF following the modular intervention as 15%, 80% power, 95% Confidence Interval, 1:1 allocation and along with addition of 20% non-response error, the total sample size will be
**60** subjects.

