### Eligibility criteria

Fathers of infants and young children with poor involvement in IYCF in households in Dakshina Kannada District will be selected for this study. Initial assessments of all fathers from selected households (see
*Study population)* will be conducted to assess fathers’ knowledge, attitude and practices towards IYCF (see questionnaire in
*Extended data*
^27^). Fathers with scores in the lower 50
^th^ percentile in the practice domain will be categorized as fathers with poor involvement in IYCF and will be eligible for inclusion in the RCT.

Those fathers who are not available for interventions despite three attempts of contact will be excluded. To promote retention of the participants, visits will be made to them at a convenient time and location. 

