### Sampling strategy and randomization

The study participants will be identified using multi-stage random sampling technique, wherein from each of the five Taluks of the District equal number of participants will be selected irrespective of their locality (urban or rural). Within each Taluk, one Public health institution and in the area covered by that institution, one ward (an administrative unit) will be selected using lottery technique. List of participants will be obtained from these public health institutions and number of participants from each selected ward will be decided based on probability proportionate to size. In the wards, they will be selected using convenience method till the required sample size gets covered.

Based on the findings from initial assessment at the district for level of knowledge, attitude and practices towards paternal involvement in IYCF, the areas with fathers of infants with poor IYCF practices will be mapped for visits at their households. Selected eligible participants will be allocated to modular intervention and control groups. A simple randomization technique with 1:1 allocation will follow. A lottery technique will be used for randomization, until the needed sample size is reached, with the help of Microsoft Excel software. The principal investigator will generate the sequence for randomization and another author (NK) will enroll the participants according to this sequence. The research assistants will implement the modular intervention.

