### Data analysis

Results will be expressed as proportions, mean (with standard deviation), median (with interquartile range), using appropriate tables and figures. We will follow intention to treat analysis (ITT). The comparison for the continuous variables will be done using the “t” tests. For comparison across the groups, Chi square tests and Multiple Logistic Regression will be used and p<0.05 will be considered statistically significant.

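### The total of 60 contradicts the abstract's 120, and the 80% power claim fails if 15% means percentage points (60 at any control proportion, 120 except at the extremes) and cannot be checked if it means a score difference

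*Protocol article*

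**What the plan says.** The Sample size section of the protocol article sets out its inputs: "With anticipated improvement in the paternal involvement of IYCF following the modular intervention as 15%, 80% power, 95% Confidence Interval, 1:1 allocation". It continues "along with addition of 20% non-response error, the total sample size will be" and gives 60 as the total. The abstract differs: "This randomized control trial (n=120) will be conducted among fathers of infants".

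Three other sections bear on how the 15% can be read:

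- **Eligibility criteria.** Fathers in the lower half of the baseline practice score are enrolled: "percentile in the practice domain will be categorized as fathers with poor involvement in IYCF and will be eligible for inclusion in the RCT". The Intervention procedure section says that involvement at six months is assessed by the same method as at baseline.
- **Outcomes.** The outcomes are knowledge, attitude and practice scores. No six-month endpoint of being above the cut-off is defined.
- **Data analysis.** Both t tests for continuous variables and chi-square tests with logistic regression are listed, with "p<0.05 will be considered statistically significant".

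The article prints neither a control proportion nor a standard deviation for the sample size.

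**The concern.** The article gives two totals, one twice the other, and attaches 80% power to the smaller. An improvement expressed as a percentage, with no SD beside it, together with a poor-involvement category and chi-square and logistic analyses, suggests a comparison of two proportions. On that scale a 15-point difference normally needs far more than 60 people. If so, a null result could be read as reasonable evidence against a 15-point benefit when the trial had little chance of detecting one. The point estimate and its interval would not be biased. What would be wrong is the stated ability of the trial to answer its question.

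**Working it through.** **Inputs.** Difference 15%, power 80%, 1:1 allocation and 20% non-response come from Sample size. Alpha 0.05 comes from Data analysis; two-sided is inferred from the 95% confidence level. The totals are 60 (Sample size) and 120 (Abstract). With 20% loss, 60 leaves 24 evaluable per arm and 120 leaves 48.

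**1. Trying to reproduce the stated total, 15 percentage points.** The pooled two-proportion formula is

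n per arm = [1.96·√(2p̄(1−p̄)) + 0.8416·√(p1(1−p1) + p2(1−p2))]² / (p2−p1)².

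The most favourable case is 0% v 15% (or its mirror, 85% v 100%). With p̄ = 0.075:

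n = (0.7301 + 0.3005)² / 0.0225 = 47.2, so 48 per arm.

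Allowing for loss, 48/0.8 = 60 per arm, or 120 in total. This reproduces the abstract's figure and not the Sample size figure. No pooled or unpooled formula that was tried gives a total of 60; the smallest was 88 (one-sided, unpooled, inflated by 1.2). The arcsine formula at exactly 0% v 15% gives 24.8, so 25 per arm, and 25 × 1.2 = 30 per arm, or 60 in total. Actual power with 25 per arm is only about 52–53%.

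**2. Power for a 15-point difference (pooled formula).**

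| Control proportion | 60 enrolled, 24/arm | 60, no loss, 30/arm | 120 enrolled, 48/arm | 120, no loss, 60/arm |
|---|---|---|---|---|
| 0% (or 85%) | 50.5% | 60.1% | 80.7% | 88.7% |
| 1% | 46.0% | 55.1% | 75.8% | 84.7% |
| 2% | 42.3% | 50.9% | 71.4% | 80.8% |
| 5% | 34.5% | 41.7% | 60.6% | 70.5% |
| 20% | 21.0% | 25.2% | 37.5% | 45.2% |
| 42.5% (worst) | 17.6% | 21.0% | 31.0% | 37.4% |

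Exact power of the uncorrected chi-square test at 0% v 15% is 49.5% with 24 per arm and 67.8% with 30 per arm, so 60 still falls short. With 48 per arm it is 94.3% at a control proportion of 0%, 80.7% at 2% and 65.6% at 5%.

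**3. Is a control proportion near 0% plausible?** All randomised fathers start below the median of a measured score and are re-measured in the same way. If the two measurements are bivariate normal with test-retest correlation r (an assumption; the article gives no r), the share of untreated fathers above the original median at re-test is arccos(r)/π.

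| r | Controls above cut-off | Power, 120 enrolled | Power, 60 enrolled |
|---|---|---|---|
| 0.6 | 29.5% | 33% | 19% |
| 0.7 | 25.3% | 34% | 19% |
| 0.8 | 20.5% | 37% | 21% |
| 0.9 | 14.4% | 43% | 24% |

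Even r = 0.99 gives 4.5%. A share of about 2% needs r of about 0.998.

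**4. Score reading.** The difference detectable at 80% power is (1.96 + 0.8416)·√(2/n) SD. For 48 per arm this is 0.57 SD; for 24 per arm, 0.81 SD. A difference of 15 is therefore detectable if the SD is at most 15/0.572 = 26.2 (120 enrolled) or 15/0.809 = 18.5 (60 enrolled), in whatever units the difference is 15. The article does not allow this to be checked.

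**5. Detectable difference if a binary level is kept.** Solving the formula in step 1 for the difference at control proportions of 20–30% gives 26.6–28.0 points with 48 per arm and 38.5–39.5 points with 24 per arm.

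**The case against.** The strongest objection is that the proportion reading is not the protocol's own. The median cut-off is an eligibility rule only, the named outcomes are scores, and t tests are listed. On a score scale either 60 or 120 could deliver 80% power. A condensed article need not print the SD or control proportion behind its calculation, and leaving them out does not show that none was used. This stands. A reader might infer that the trial definitely lacks its stated power, and the document does not support that.

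Two further points also stand in part. It would be too strict to say that 120 works only if literally no control father crosses the cut-off: with no loss, or by exact chi-square power with the planned loss, about 2% is tolerated. And since every father enters below the cut-off, the authors may have assumed 0% in controls. A reader might then conclude that 60 is simply the per-arm number. That is plausible, because 0% v 15% gives exactly 60 per arm after loss, but it remains an inference.

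The objection does not remove the conflict between 60 and 120, and it does not rescue 60 on the proportion scale.

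**Conclusion.** The sample-size statement is wrong as written, because the two totals cannot both be right. The power claim attached to them depends on the scale of the 15%:

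- **Percentage points:** 60 cannot give 80% power at any control proportion. 120 gives it only at or very near 0% in controls or 100% in the intervention arm. Such proportions are unlikely in a group selected below a median and re-measured. The 33–43% (120) and 19–24% (60) figures rest on bivariate normality and r of 0.6–0.9, neither of which is in the document.
- **Mean score:** the claim is unverifiable, not shown false. It holds if the SD is small enough.

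The two-proportion arithmetic is firm; which scale the authors meant is not known from the article.

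**What to change.** Rewrite the Sample size paragraph and align the abstract with it:

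1. Replace 60 and 120 with the number actually randomised. The section on current status says recruitment is complete, so this is known.
2. Name the scale of the primary comparison.
3. Replace the 80%/15% statement with the effect detectable at 80% power, two-sided 5%, after 20% loss. For the practice score this is about 0.57 SD (120 enrolled, 96 evaluable) or 0.81 SD (60 enrolled, 48 evaluable). If a binary level is kept, define it at six months and state about 27–28 points (120) or 39 points (60) at assumed control proportions of 20–30%.

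If the original calculation was on the score scale, giving its SD and units would let the 15% be checked.

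Cost: one paragraph and one figure in the abstract, with no extra participants. The stated detectable effect becomes less favourable.

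### The abstract gives the randomised trial as 120 fathers and the Sample size section gives a total of 60; the protocol does not reconcile the two

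*Protocol article*

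**What the plan says.** The protocol article gives the size of the trial twice.

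- **Abstract, Methods:** "This randomized control trial (n=120) will be conducted among fathers of infants". The number is attached to the randomised trial. The baseline assessment that precedes it is mentioned separately and carries no number.
- **Methods, Sample size:** the inputs are "With anticipated improvement in the paternal involvement of IYCF following the modular intervention as 15"%, then "80% power, 95% Confidence Interval, 1:1 allocation", and then "along with addition of 20% non-response error, the total sample size will be" 60 subjects.

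Two other sections bear on the point. Sampling strategy and randomization says that random allocation continues "until the needed sample size is reached", without a number. Current status of the study says that recruitment has finished and four monthly rounds of the module have been delivered; it does not say how many fathers were randomised.

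**The concern.** The two statements describe the same randomised trial and differ by a factor of two. The Sample size section calls 60 the total after it has already named the allocation ratio and the 20% addition, so no later step in that section turns 60 into 120.

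The planned total is the figure against which a results paper is read. It shows whether the trial reached its size, what precision was intended, and how large any shortfall was. With two totals on record, 60 fathers randomised would be full recruitment under one and half recruitment under the other, and this article cannot tell the reader which.

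**Working it through.** **1. Direct comparison**

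| Place | Figure | Described as |
|---|---|---|
| Abstract | 120 | size of the randomised trial, 1:1 |
| Sample size | 60 | total, 1:1, after the 20% addition |

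120/60 = 2. No other section calls 60 a per-arm number or gives 120 another meaning.

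**2. Can either figure be reproduced from the stated inputs?**

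Stated: 15% improvement, 80% power, 95% confidence, 1:1, 20% addition; Data analysis adds "p<0.05 will be considered statistically significant". Not stated: control rate or SD, whether 15% is absolute or relative, whether the endpoint is a proportion or a score, one- or two-sided, and how the 20% is applied. Neither figure therefore follows uniquely. The two routes below rest on assumed inputs.

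*Route to 120 (60 per arm).* Assume 0% versus 15%, two-sided 5%, pooled formula:

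n = [1.960·√(2·0.075·0.925) + 0.842·√(0·1 + 0.15·0.85)]² / 0.15²

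= [1.960·0.3725 + 0.842·0.3571]² / 0.0225 ≈ 47.2, rounded up to 48 per arm.

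48/(1 − 0.20) = 60 per arm, 120 in total.

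*Route to 60 in total.* Assume the same 0% versus 15%, arcsine formula:

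h = 2·arcsin(√0.15) − 0 = 0.795

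n = 2·(2.802/0.795)² ≈ 24.8, rounded up to 25 per arm.

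25 × 1.2 = 30 per arm, 60 in total.

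The first route matches 120 exactly and makes a mislabelled per-arm number plausible. The second shows that a true total of 60 is also reachable. Both depend on an assumed control rate of 0%; at 1%, the pooled route already gives 68 per arm, 136 in total.

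**3. What the factor of two means**

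Confidence-interval width is proportional to 1/√N, so the ratio is √(120/60) = √2 = 1.41. This needs no assumption about the endpoint, provided the same proportion of fathers is lost at either size.

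*Illustration only*, assuming a two-sample comparison of mean scores, two-sided 5%, 80% power, normal approximation:

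detectable difference = (1.960 + 0.842)·√(2/n), n per arm, in SD units

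| Reading of the 20% | n per arm at 60 / 120 | Detectable difference at 60 / 120 |
|---|---|---|
| 20% lost after randomisation | 24 / 48 | 0.81 / 0.57 SD |
| total inflated as n × 1.2 | 25 / 50 | 0.79 / 0.56 SD |
| no loss after randomisation | 30 / 60 | 0.72 / 0.51 SD |

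Calculating with the t distribution instead raises these slightly (0.83 / 0.58 SD in the first row, 0.74 / 0.52 SD in the last).

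**The case against.** Five points can be made on the other side.

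- **Recruitment is over.** A reader might infer that the end of randomisation is left open between 60 and 120. That cannot be pressed as a live risk: Current status of the study reports recruitment complete, so a corrected sentence changes nothing about when randomisation stops. This stands, and it limits the harm to reporting and interpretation.
- **Other records may settle the number.** A reader might infer that either figure could later be presented as the planned one. The article cites a trial registration, a CONSORT flow chart and a SPIRIT checklist, none of which is at hand, and any of them may fix the figure. The inference is conjecture and is not made here. The article is still wrong in one of its two places.
- **Evaluable numbers are not in the plan.** A reader might take 24 or 48 per arm as the plan's own evaluable numbers. The wording is "addition of 20% non-response error", which could equally mean multiplication by 1.2, or refusal before enrolment with no stated loss afterwards. The SD figures also presuppose a comparison of means, which the Sample size section does not specify. This stands, and those figures are offered only as illustration.
- **No calculation is shown to be wrong.** Since the inputs are incomplete, neither 60 nor 120 can be called an arithmetic error, and the text does not establish that 60 is per arm. This stands. The finding is an internal contradiction.
- **The two numbers might count different things.** Eligibility takes fathers in the lower half of the practice score, so 120 assessed and 60 eligible is numerically possible. This is the weaker reading, because the abstract attaches 120 to the trial itself. It is still a reason to ask the authors what each number counts.

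**Conclusion.** The contradiction is real and can be read directly from two sentences: 120 for the randomised trial in the abstract, a total of 60 in the Sample size section. At least one is wrong as written. The size is two-fold in N and a factor of 1.41 in confidence-interval width. Under the added assumptions of a mean-score comparison and 20% loss after randomisation, the detectable difference is about 0.81 SD versus 0.57 SD; with no loss it is about 0.72 versus 0.51 SD.

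A mislabelled per-arm number is a plausible explanation, but it rests on an assumed 0% control rate and the document does not confirm it. Only the authors can say which figure was planned. Whether either size is adequate for a 15% improvement is a separate question on which this point does not depend. The contradiction must be resolved before results are reported.

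**What to change.** State one planned total, with its per-arm number, in both the abstract and the Sample size section:

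- if 60 was meant per arm, the Sample size section should read 60 per arm, 120 in total;
- if 60 was meant as the total, the abstract should read n=60, 30 per arm;
- if the two numbers count different things, such as fathers assessed and fathers randomised, say so and label each.

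Say what the 20% addition represents and how it was applied before giving any evaluable number. Because recruitment is complete, report the planned total beside the number actually randomised and state any difference.

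The cost is a corrected sentence in one or both sections and one line in the results report. No extra participants and no change to trial conduct are needed.
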